### Trial design (12)

This is a randomized trial with two parallel intervention arms. Participants will be randomly assigned to either the Behavioral Activation (BA) group or the Cognitive Restructuring (CR) group in a 1:1 ratio. The primary goal of the study is to determine (1) which baseline characteristics predict the benefits (in terms of reduction of depression symptoms) each individual participant will receive from CBT-based interventions, and (2) which baseline characteristics moderate the therapeutic effects of BA and CR. Therefore, the study does not fall in the categorization of superiority, non-inferiority, or equivalence framework, and we do not make any assumptions regarding differences in overall treatment efficacy. We do not plan to establish efficacy, safety of feasibility. Instead, this is a mechanistic clinical trial aiming to uncover moderation of intervention effects.

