Second, we will add task-derived variables from each task separately to the baseline model to test whether these variables improve the predictive accuracy. For each set of task variables that we find to improve predictive accuracy, we will preregister the corresponding analyses for confirmation in the test dataset. We take this single-task approach as we consider each task as a separate instrument to be tested for efficacy independently, and to improve clinical feasibility (as one 15-minute task is clinically more feasible than a two-hour task battery) and interpretability (as some tasks assess correlated features, so combining them could obscure which variables drive the effects).

We will take this two-step approach both when examining how well we can predict whether an individual will respond to CBT-based interventions, and whether we can differentially predict whether they will benefit more from BA vs CR. For algorithms aiming to predict depression scores at week six after engaging with any CBT-based interventions, the final outcome will be out-of-sample predictive accuracy above chance (for the baseline model) or above the baseline model (for models including task data). For algorithms predicting differential outcome for behavioral vs. cognitive interventions, we will train algorithms for each arm separately. Following the approach of the personalized advantage index (PAI; 88, 89), we will use the model to predict for each participant the outcome for the intervention they received (using models trained on data not including this participant) and for the one they did not receive (counterfactual outcome). The final outcome will constitute whether individuals who were predicted to have received their more beneficial outcome have lower depression scores at the 6-week mark than those who the algorithm predicts would have fared better from the other intervention (and how much that difference improves by adding in task parameters).

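### The success criterion for choosing between BA and CR can be met by a plain average difference between the arms, with no moderation

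*Protocol article*

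**What the plan says.** Section 12 (Trial design) names as its second primary goal "which baseline characteristics moderate the therapeutic effects of BA and CR". It adds that "we do not make any assumptions regarding differences in overall treatment efficacy".

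Section 27a (Primary analyses) gives the method: "For algorithms predicting differential outcome for behavioral vs. cognitive interventions, we will train algorithms for each arm separately". Following the personalized advantage index (PAI), each participant receives a predicted outcome under the arm received and under the other arm. The final outcome is then "whether individuals who were predicted to have received their more beneficial outcome have lower depression scores at the 6-week mark". The comparison group is the participants allocated to the arm that the models did not favor for them. A second limb asks "how much that difference improves by adding in task parameters".

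For this outcome, section 27a sets no comparison with giving everyone one arm, retains no arm main effect, and includes no interaction between the PAI and arm.

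**The concern.** The aim is moderation, but the contrast responds to two different things: real differences between people in which arm suits them, and a constant advantage of one arm. Because the models are fitted separately by arm, a constant advantage enters every participant's PAI. Once it is large relative to the estimation noise, the recommendation is the same for almost everyone. Those who received the recommended arm are then simply those allocated to the better arm.

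The trial could then report a working selection algorithm when the right conclusion is that one arm is better for everybody. Section 12 does not rule this out, since it takes no position on the average difference.

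**Working it through.** **Inputs from the protocol.** Allocation 1:1 (section 12). Training set 1,000, test set over 300, attrition about 20%, 4–6 predictors, shrinkage 0.9, Cox-Snell R² 0.05 (section 19). Recruiting 1,500 and losing 20% leaves 1,200, which splits 2:1 into 800 and 400, so a test set of 400 was also examined.

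**Plan's own figure.** The protocol gives no figure for this contrast. Its development sample size reproduces with 5 predictors: 5 / [(0.9 − 1) × ln(1 − 0.05/0.9)] = 874.8, hence 875.

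**Assumptions, not in the protocol.** Outcome SD 1; prognostic R² 0.3; zero moderation; average arm difference d from 0 to 0.4 SD; two-sided 5% test counted only in the favorable direction (nominal 2.5%).

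**Algebra.** Let δ be the constant advantage of the better arm and q the share of participants recommended it. Under 1:1 randomization, receiving the recommended arm has probability 1/2 at every covariate value. Relative to everyone receiving the better arm:

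- mean excess score, received recommended arm: δ(1 − q)
- mean excess score, did not: δq
- difference: δ(1 − q) − δq = −δ(2q − 1)

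This is zero only if δ = 0 or q = 1/2. As q approaches 1 it becomes −δ, the plain BA–CR difference. Check at d = 0.2, test N = 400, 6 predictors: simulated q = 0.91, so −0.2 × (2 × 0.91 − 1) = −0.164; the simulated contrast was −0.163.

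**False-success rate with zero moderation** (separate models per arm, scored on held-out data; 2,000 runs for least squares, 200 for lasso):

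| Setting | d = 0 | 0.1 | 0.2 | 0.3 | 0.4 |
|---|---|---|---|---|---|
| 6 predictors, test 300 | 2.5% | 7.4% | 32.8% | 68.1% | 93.1% |
| 6 predictors, test 400 | 3.0% | 7.2% | 39.4% | 79.2% | 97.2% |
| 20 predictors, test 300 | 2.2% | 4.6% | 19.0% | 53.3% | 86.0% |
| Lasso, 6 predictors, test 300 | 1.5% | 7.5% | 36.5% | 72.0% | 94.0% |

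A separate set of runs with 6 predictors gave about 7%, 30%, 72% and 92% at d = 0.1 to 0.4 with 300 test participants, and 9%, 36%, 80% and 98% with 400.

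**The mechanism is visible.** In the first row the better arm is recommended to 77% of participants at d = 0.1, 93% at 0.2, 98% at 0.3 and over 99% at 0.4. The power of a plain two-arm comparison at N = 300 is 13.7%, 41.0%, 73.8% and 93.4%, and the false-success rate climbs to meet it. With 20 predictors the PAI is noisier, recommendations are less uniform and the rates are lower.

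**The second limb.** Adding three pure-noise task variables changed the contrast by −0.001 to +0.015 SD on average, which is no improvement.

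**Alternatives under the same zero-moderation settings.** The PAI-by-arm interaction with the arm main effect retained rejects in 1.8–3.3% of least-squares runs at every d; the lasso figures, 2.0–4.5%, rest on 200 runs. Comparing the PAI policy with the single better arm, chosen in training, rejects in at most 2.9%.

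**Power with real moderation** (slope difference 0.5 SD per SD of one predictor, test N = 300):

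| Test | d = 0 | d = 0.2 |
|---|---|---|
| Stated contrast | 91.0% | 94.3% |
| PAI-by-arm interaction | 98.5% | 98.3% |
| Policy versus better single arm | 66.3% | 33.6% |

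**The case against.** **The approach is declared provisional.** Section 27 presents these methods as the best identified so far and allows a less biased one to replace them; section 16 leaves precise estimands to the preregistration. This stands in part: nothing is yet irreversible. But 27a already names the final outcome, and following it as written leads to a wrong conclusion whenever the arms differ appreciably.

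**Other moderation analyses are planned.** The mechanisms-of-change subsection asks whether specific variables affect response to only one intervention. That is a partial safeguard. It concerns task variables and is not a condition for calling the selection model successful.

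**The arms may be equally effective.** The introduction cites comparable efficacy across therapy components, and both arms share a platform, first-week psychoeducation and similar dose. If they are equal, the error rate is nominal. Section 12, however, assumes nothing either way, and only BA includes the physical activity module.

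**Stronger readings that a reader might infer:**

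- *That the claimed added value of the tasks is also spurious.* An average difference is already in the baseline model, and noise task variables did not improve the contrast.
- *That ignoring baseline PHQ-9 biases the contrast.* Under 1:1 randomization it does not; adjustment gains precision only.
- *That any interaction test settles the matter.* An interaction can be present while one arm is still better for everyone, which is why a policy comparison is also needed. A binary recommendation-by-arm term also loses power when recommendations are lopsided: in one simulated case with real moderation and d = 0.4, 0.22 against 0.72 for the continuous PAI. Those two values depend on the moderation strength assumed, so only their order should be relied on.

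**Conclusion.** The concern holds for the stated contrast. With zero moderation, about 6 predictors and 300 test participants, false success against a nominal 2.5% is about 7% at an average difference of 0.1 SD, 30–33% at 0.2, 68–72% at 0.3 and 92–93% at 0.4. It is somewhat higher with 400 from 0.2 SD upward, and lower with 20 predictors. The inflation is small at 0.1 SD and serious from about 0.2 SD.

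The algebra needs only 1:1 allocation and a constant arm effect. The percentages rest on the assumed SD, prognostic strength and test level, and on least-squares and lasso models; random forests, also planned, were not simulated. The size of any BA–CR difference is unknown, so this is a vulnerability of the criterion and not a prediction that the trial will mislead.

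It is confined to the claim that the selection model works, chiefly the clinical and demographic baseline model.

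**What to change.** Before the test set is accessed, in section 27a and the preregistration:

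1. Define success in differential prediction as the continuous PAI-by-arm interaction in the test set, with the arm and PAI main effects retained and baseline PHQ-9 included for precision. This is the evidence of moderation.
2. For any claim that selection helps, compare the mean outcome under the recommended policy with giving everyone the single better arm, that arm being chosen in the training data.
3. Report the present recommended-versus-non-recommended difference as descriptive only.

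The cost is protocol and preregistration wording and one or two extra preregistered analyses. No new data are needed. The policy comparison is less precise when recommendations are lopsided: in the moderation scenario above its power fell from 66.3% at d = 0 to 33.6% at d = 0.2. That loss reflects how little selection can add when one arm already suits most participants.

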### Sample size (19)

We computed the required sample size for a multivariable prediction model with binary outcomes based on Riley et al. (39). To our knowledge, previous models are not available in the literature to anticipate Cox-Snell R2 for our study. Hence, we estimated the required Cox-Snell R2 value to be 0.05 based on pseudo-R2 values from the field of computational psychiatry, assuming small effect sizes when relating task behavior to symptom measurements (40, 41). Note, however, that this is a very conservative estimate, as we have previously found a large effect size when relating parameter estimates from the planned effort task to clinical diagnoses and a medium effect size when relating the parameters to subsequent symptom development (28). Furthermore, as we have optimized our tasks to relate to symptom changes due to therapy, we expect larger effect sizes in this study. For the sample size calculation, we also assumed a prevalence of response to iCBT of 0.5 (42), setting the shrinkage parameter to 0.9 to avoid overfitting 4–6 predictors (parameter estimates from our tasks and candidate predictors from the literature such as baseline severity (43) and gender (42)). The computed required sample size is 875 participants. We have therefore conservatively planned for a training set sample size of N = 1000. For current planning purposes, we assume that we will dedicate data from over 300 participants to the test dataset, well exceeding the recommendations for 100–200 events for validation data sets (44). Anticipating an attrition rate of approximately 20% (45, 46), we aim to recruit a total of 1,500 participants based on power analysis. We will compute the power that our test dataset provides once we have obtained results from our model development (47).

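### For the BA-versus-CR aim, a task's added value is read from the change in a sign-split PAI contrast, which is an insensitive test of whether the task improves differential prediction

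*Protocol article*

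**What the plan says.** Protocol article, section 27a (Primary analyses). For the differential aim, "we will train algorithms for each arm separately", and each participant receives a predicted outcome for the arm received and for the other arm, following the personalized advantage index (PAI). The final outcome for this aim is whether "individuals who were predicted to have received their more beneficial outcome have lower depression scores at the 6-week mark" than those predicted to do better with the other arm, together with "how much that difference improves by adding in task parameters". The sequence is a clinical and demographic baseline model first; then "we will add task-derived variables from each task separately to the baseline model".

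The same section lists mean squared error, R², balanced accuracy and AUROC for the predictive models generally. It names no measure that uses the size of the predicted advantage as the final outcome of the differential aim. The next subsection, on mechanisms of change, plans separate moderation analyses.

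Section 19 plans on small task effects ("assuming small effect sizes when relating task behavior to symptom measurements") and postpones the power of the test set. Sections 16 and 27 leave estimands, significance levels and code to a later preregistration, and section 27 allows a different approach if a more suitable one is found.

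**The concern.** The PAI is a continuous quantity, but this outcome uses only its sign. A participant whose recommended arm is the same with and without the task falls in the same group in both contrasts and nearly drops out of the difference between them. The change therefore rests on those who switch. Switchers tend to have a predicted advantage near zero, so little benefit is at stake for each of them.

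Whether learning tasks improve prediction is one of the study's stated goals, and the held-out test set can serve for confirmation only once. If the change in the contrast were used as the test of a task's increment, a task that truly moderates response could easily show no clear improvement, although the same data hold enough information to detect it.

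**Working it through.** **The plan's own figure.** Section 19 uses the shrinkage criterion n = P / [(S − 1) ln(1 − R²/S)]. With S = 0.9, Cox-Snell R² = 0.05 and P = 5, n = 5 / [0.1 × 0.05716] = 874.8, so 875, as stated (P = 4 gives 700; P = 6 gives 1,050). This sizes a binary response model ("we also assumed a prevalence of response to iCBT of 0.5"), not the PAI contrast or its change.

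**Inputs.** From the protocol: 1,500 recruited, about 20% attrition, 2:1 training to test, 1:1 arms. Hence 1,500 × 0.8 / 3 = 400 test participants (the protocol says over 300). Assumed, because the protocol gives no figure: two-sided alpha 0.05, residual SD 1, no average arm difference, and a task whose contribution to the individual BA–CR difference has SD s_t = 0.28. The baseline model's contribution has SD s_b, varied from 0 to 2 × s_t.

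**Interaction test.** z = √n × s_t / 2 = 20 × 0.14 = 2.8; power = Φ(2.8 − 1.96) = 80%.

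**Change in the sign-split contrast.**
- Share switching: p = arctan(s_t/s_b)/π.
- Expected change: g = √(2/π) × [√(s_b² + s_t²) − s_b].
- Standard error: 4√(p/n). Power = Φ(g/SE − 1.96).

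| s_b / s_t | p | g | SE | z | Power of the change |
|---|---|---|---|---|---|
| 0 | 0.50 | 0.223 | 0.141 | 1.58 | 35% |
| 0.5 | 0.35 | 0.138 | 0.119 | 1.16 | 21% |
| 1 | 0.25 | 0.093 | 0.100 | 0.93 | 15% |
| 2 | 0.15 | 0.053 | 0.077 | 0.69 | 10% |

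Simulation with true benefit scores gave 34%, 20%, 15% and 10%, against about 79% for the interaction.

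**The task model's own contrast.** z = √(2/π) × √(s_b² + s_t²) / (2/√n). For s_b = 0 this is 0.798 × 0.28 / 0.1 = 2.23, power 61%. For s_b = 2 × s_t it is 0.798 × 0.626 / 0.1 = 5.0, power above 99%.

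**Estimated models.** Separate linear models per arm, 800 training and 400 test participants, 1,000 replicates, prognostic R² 0.3:

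| Task-interaction R² | Change, baseline moderation equal to task | Change, no baseline moderation | Continuous interaction |
|---|---|---|---|
| 0.01 | 0.09 | 0.15 | 0.50 |
| 0.02 | 0.13 | 0.29 | 0.81 |
| 0.03 | 0.19 | 0.43 | 0.94 |
| 0.05 | 0.25 | 0.64 | 0.99 |

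Across 16 scenarios (R² 0.01 to 0.05, baseline-to-task ratio 0 to 2) the change had power below 0.50 in 15, and in 13 after prognostic adjustment. The exceptions had R² of 0.03 or more and little or no baseline moderation. The change correlated 0.998 to 0.999 with the sum over switchers alone, so non-switchers enter only slightly, through group sizes. With no task effect both methods rejected at about 2% in the upper tail, so the interaction's advantage is not bought with false positives.

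**Sensitivity (closed form, R² 0.02, equal moderation).** The change has 13% power at n = 300 and 18% at n = 500, against 70% and 89% for the interaction. One-sided at n = 400 it has 24%.

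**The case against.** Four points on the other side carry weight.

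- **The contrast answers a clinical question.** A task that leaves someone's recommended arm unchanged has no treatment-selection value for that person. Low power partly reflects a small gain: 0.05 to 0.14 residual SD where the baseline model has some moderation. This stands. The change is a legitimate estimate of selection value, so the documents give no ground for discarding it. It remains a poor test of whether the task improves differential prediction.
- **No decision rule is stated.** A reader might infer that the trial will test the change and take a non-significant result as evidence against its hypothesis. The protocol says neither: it asks how much the difference improves, and leaves tests and significance levels to preregistration. But the quantity itself is already written down as the final outcome, so the time to supplement it is before that preregistration.
- **Moderation analyses are planned.** They bear on the same arm-by-task question. They are presented as explaining mechanisms, not as the final outcome of the differential aim, and no test-set regression on the predicted advantage is described.
- **The effect sizes are assumed.** A reader might infer that a real task effect will usually be missed. That needs interaction sizes, baseline moderation and an alpha that the protocol does not give. With no baseline moderation and R² 0.05, power reaches 0.64 with estimated models and 0.74 in closed form.

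**Conclusion.** The point holds as a matter of sensitivity. At a task effect where the interaction has about 80% power in 400 test participants, the change in the sign-split contrast has about 10% to 35%. It exceeds 50% only with a large task interaction and little baseline moderation. These figures rest on two-sided alpha 0.05, linear effects and the moderation sizes shown; penalised and forest models were not part of these calculations.

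A reader might go further and conclude that the BA-versus-CR claim itself is lost. The figures do not support that: the task model's own contrast has 61% to over 99% power in the closed-form settings, and about 70% with estimated models at R² 0.02 and equal baseline moderation. That contrast cannot, however, show that the task added anything over the baseline model. This is a cheap improvement to the preregistration, not a flaw that invalidates the design.

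**What to change.** In the preregistration, test the task increment in the test set by regressing the week-6 score on arm, the baseline model's continuous predicted advantage, the task-added part of the predicted advantage (task model minus baseline model), and the interaction of arm with each. The arm-by-task-part term is the test of the increment.

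Keep the difference between those who did and did not receive their predicted-better arm, and its change when a task is added, as the estimate of clinical benefit, with confidence intervals. State that a non-significant change is not evidence that the task adds nothing.

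The cost is wording and code, with no new participants or data. The downside is that the interaction term is less directly clinical: it shows moderation, not the size of the treatment-selection gain. Both results therefore have to be reported.

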#### Uncovering mechanisms of change

To understand in detail how specific task variables relate to changes in symptoms, we will run two types of analyses. We will conduct moderation analyses to examine whether specific variables only influence response to one, but not the intervention. For tasks that were assessed a second time during the interventions, we will use mediation analyses to test whether change in specific task variables by the middle of the intervention can account for the change in symptoms by the end of the intervention.

### Who will be included in the analyses (27b)

For all analyses, we will include only participants who (a) met the assessed inclusion and exclusion criteria specified in Section 14a, *Eligibility criteria*, and (b) passed identity and attention checks at the beginning of the study. For predictive modeling and causal inference, the analytic sample will include participants who were randomized and had a baseline PHQ-9 total score greater than 4. This constitutes our intention-to-treat (ITT) sample.

### How missing data will be handled (27c)

We anticipate a low proportion of missing data from self-report questionnaires and behavioral tasks from baseline as data collection is automated and participants can only advance after completing all components within a batch, i.e., such missing data will be missing completely at random (MCAR). Nevertheless, technical issues may occasionally result in missing data. We will impute missing data for questionnaires and task data using recommended imputation procedures such as Multivariate Imputation by Chained Equations (MICE, 90). Imputation will be applied for predictors and independent variables. As we assume that outcome data might be missing not at random (MNAR), we plan to not impute outcome data. However, we will examine all our assumptions about missingness mechanisms through sensitivity analyses and adjust our imputation decisions and analyses accordingly. During model development, imputation will be performed in a nested manner within the cross-validation framework such that imputation models are fit using only the training data within each fold, with no access to held-out folds. No auxiliary variables beyond the predictor set of the model under evaluation will be included in the imputation models (91). For models that make separate predictions per group, imputations will be conducted separately by intervention group (92). The finalized imputation strategy, including the predictor matrix, will be specified in the preregistered confirmatory analysis plan prior to evaluation on the held-out test dataset.

Participants who wish to do so will be permitted to skip two behavioral tasks, the (*Explicit to implicit generalization task* and the *Scream task*), which involve emotionally aversive stimuli, without withdrawing from the study. As this constitutes a case of structured missingness and imputation of task data would not add information to answer the question whether task data improves the explanatory power for outcome above and beyond baseline measures, we will not impute data for individuals who skipped these tasks. Instead, these participants will be excluded from analyses that directly involve measures derived from these tasks, but will be retained in all other analyses. To assess potential bias associated with task noncompletion, task non-completion will be explicitly coded as an indicator variable, and sensitivity analyses will be conducted comparing results with and without participants who skipped these tasks. Associations between task non-completion and symptom severity will also be examined to evaluate whether avoidance of aversive stimuli relates systematically to clinical characteristics. This is a purposeful design feature that weighs subjective feelings of discomfort of possibly vulnerable participants against building generalizable predictive algorithms. We acknowledge that the generalizability of our algorithms will have to be tested in individuals who prefer not to be exposed to negative emotional stimuli, possibly in an in-person study with more immediate clinical support if the algorithms are demonstrated to be useful. We will explicitly acknowledge in the publications of results related to these two tasks that findings may not generalize to individuals with higher avoidance or lower distress tolerance, and discuss this as a limitation.

In contrast, several questionnaires (*NEO-FFI*, *PSWQ* and *MSPSS*) and the *Symmetry* sp*am* task were introduced after the first 100 participants (in the transition from protocol version 1.0 to version 1.1 described here) and thus were not available to the initial cohort. For these tasks, all participants will be included with imputed data if data are missing.

For confirmatory analyses on the test dataset, missing-data procedures will be finalized and preregistered before accessing the held-out test dataset to ensure analytic independence.

